**Objective:**

The study aims to evaluate the impact of a mobile health intervention based on the Behavior Change Wheel theory and Family Health Theory on prenatal diagnostic participation rates and pregnancy outcomes in high-risk pregnant women, while exploring the role of family member involvement in improving maternal psychological health and pregnancy outcomes.

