### Design

2.1

This study is a single-blind, interventional randomized controlled trial conducted at the Inner Mongolia Maternity and Child Health Care Hospital. The aim is to evaluate the impact of a mobile health intervention based on the Behavior Change Wheel theory and Family Health Theory on the prenatal diagnosis rate and pregnancy outcomes of high-risk pregnant women undergoing prenatal screening. The study will be conducted from June 2025 to June 2026. The flowchart of the study is shown in **Figure 3** and **4**.

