### Sample size estimation

2.3

This study is a randomized controlled trial, where the intervention group will receive the mobile health intervention and the standard care group will receive standard care. The outcome measure is the prenatal diagnosis demand. Based on previous randomized controlled trials related to willingness to undergo screening for related diseases, the intervention group’s demand proportion is 53.4%, and the standard care group’s is 34%, showing an increase of approximately 19.4% (28). We predict that the mobile health intervention based on the Behavior Change Wheel theory and Family Health Theory may lead to a doubling of the demand proportion (38.8%), reaching 72.8% (29). The expected demand proportion for the intervention group is 72.8%, and for the standard care group is 34%. Using a two-sided test with α = 0.05, β = 0.2, and power (1-β) = 80%, the sample size ratio between the two groups is 1:1. After using the PASS software (version 2021) to calculate the relevant values, it was determined that 23 participants per group would be required. Considering a 20% dropout rate, the final sample size for each group is 29 participants, for a total of 58 participants.

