**Phase 2: Appointment scheduling and family support (Week 5-8)**

**Responsible personnel**: A team consisting of 2 nurses, 1 social worker, 1 psychologist, and 1 genetic expert.
**Competencies**: The nurses will guide participants in scheduling their prenatal diagnosis appointments, the social worker will facilitate family communication and ensure family members understand their supportive roles, the psychologist will provide emotional support and counseling to help manage anxiety and emotional concerns, and the genetic expert will provide specialized input on prenatal diagnosis and genetic counseling.
**Process**: During this phase, the nurses will assist pregnant women and their families in scheduling prenatal diagnosis appointments and provide support to ensure they understand the entire process. The social worker will educate family members on how to emotionally and physically support the pregnant woman. The genetic expert will host online lectures for the families to answer questions about the diagnostic process and boost their confidence in prenatal diagnosis. Each session will last 45 minutes and will be scheduled bi-weekly. The social worker will also send customized reminders to each family in the WeChat group, reminding them of the upcoming prenatal diagnosis appointment and key details while encouraging emotional regulation, such as, “Dear XX family, your prenatal diagnosis appointment is approaching, please be prepared and maintain a positive mindset!” For those who are anxious about the results or the process, the psychologist will provide counseling to help them manage their emotional concerns and complete the prenatal diagnosis with peace of mind.
**Incident management**: If a participant experiences logistical issues, such as scheduling conflicts or transportation problems, the social worker will step in to provide solutions or connect the participant with local resources to resolve these issues.

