#### Primary outcomes

2.8.1

The primary endpoints are the demand for prenatal diagnosis and pregnancy outcomes. Demand is defined as the perceived or expressed need, typically associated with changes in health status. Demand is measured at the individual level both before and after the intervention. A participant is considered to have a screening demand if they answer “yes” to at least one of the following three questions: willingness for diagnosis, plans for prenatal diagnosis within six months, or having undergone diagnosis. The overall demand is the union of these three items. For participants who report having been diagnosed, the researchers will verify the diagnosis by reviewing relevant documents or appointment cards.

Pregnancy outcomes include full-term birth, preterm birth, miscarriage, induced labor due to social factors, and induced labor due to chromosomal abnormalities.

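### The stated aim is the prenatal diagnosis rate, but the primary endpoint is met by willingness or a plan alone, and completed diagnosis is not listed as an outcome of its own

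*Protocol article*

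**What the plan says.** **Aim.** Section 2.1 (Design) says the trial evaluates the impact "on the prenatal diagnosis rate and pregnancy outcomes of high-risk pregnant women undergoing prenatal screening". The Objective in the Abstract says "on prenatal diagnostic participation rates and pregnancy outcomes in high-risk pregnant women". The Discussion (section 3) again names participation as what is assessed, and the Introduction describes the problem as high-risk women not completing confirmatory procedures.

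**Endpoint.** Section 2.8.1: "The primary endpoints are the demand for prenatal diagnosis and pregnancy outcomes". Demand is met by a yes to at least one of "willingness for diagnosis, plans for prenatal diagnosis within six months, or having undergone diagnosis", and "The overall demand is the union of these three items". Table 1 gives the same three items. For women who report a diagnosis, "the researchers will verify the diagnosis by reviewing relevant documents or appointment cards". Neither section 2.8.1 nor section 2.8.2 lists completed diagnosis as a separate outcome. The evaluation paragraph at the end of section 2.6.1 mentions tracking participation rates, but as feedback for adjusting the intervention.

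**Sample size.** Section 2.3: "The outcome measure is the prenatal diagnosis demand", with 34% expected under standard care and 72.8% under the intervention. The starting rates come from earlier trials of willingness to be screened.

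**Intervention and blinding.** In weeks 5 to 8, "the nurses will assist pregnant women and their families in scheduling prenatal diagnosis appointments". Section 2.4 calls the trial single-blind for participants, yet each woman opens the envelope that shows her group. The same section says evaluators are not blinded.

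**The concern.** The aim is a behaviour (a diagnosis carried out), while the endpoint is an expressed need that one spoken yes can satisfy. Two of the three items are intentions. The intervention works directly on them through education, encouragement, reminders and help with scheduling, and standard care as described in section 2.6.2 contains nothing comparable. Women who know they are in the programme answer to staff who also know it, and the Discussion concedes that the data are mainly self-reported.

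At stake is what a positive result would mean. The Abstract and Discussion frame the expected finding as greater participation. A significant difference in demand could arise wholly from willingness and plans, and no listed outcome would then show whether more diagnoses were done.

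**Working it through.** **1. The plan's own figure.** Inputs from section 2.3: p1 = 0.728, p2 = 0.34, two-sided α = 0.05, power 80%, 1:1 allocation. With unpooled variance:

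n = (1.960 + 0.842)² × [0.728 × 0.272 + 0.34 × 0.66] / 0.388² = 7.849 × 0.4224 / 0.1505 = 22.02, rounded up to 23 per arm.

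Dropout: 23 / 0.8 = 28.75, rounded up to 29. Both figures reproduce, so the sample size is consistent with the demand endpoint. The fault lies between endpoint and aim, not in the arithmetic.

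**2. How few answers decide the test.** With 8/23 controls meeting demand (35%, close to the planned 34%), 15/23 in the intervention arm is significant. The pooled proportion is 23/46 = 0.5, the standard error is √(0.25 × 2/23) = 0.1474, and z = (7/23)/0.1474 = 2.06. All seven extra responders could be women who said only that they were willing.

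**3. Demand rises, uptake does not.** The article gives no uptake rate, so this step is an assumption shown over a range. Demand in controls is 34%, and completed diagnosis is the same in both arms. Let c be the share of the remaining 66% of intervention women who say yes to willingness or a plan only. Intervention demand is then 0.34 + 0.66c. The table gives the exact probability that an uncorrected two-sided chi-square test is significant. That test is my choice, since the article names the chi-square test only for demographic comparisons.

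| c | Demand, intervention vs control | Difference, points | 23 per arm | 29 per arm |
|---|---|---|---|---|
| 10% | 40.6% vs 34% | 6.6 | 7.4% | 7.5% |
| 30% | 53.8% vs 34% | 19.8 | 28.2% | 32.2% |
| 50% | 67.0% vs 34% | 33.0 | 63.9% | 72.1% |
| 59% | 72.8% vs 34% | 38.8 | 78.4% | 85.8% |

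The last row follows from c = 0.388/0.66 = 0.588. A test of uptake itself, with equal assumed rates of 10%, 20% or 30% in both arms, is significant in only about 5% of trials.

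**4. Power for completed diagnosis.** Again under assumed rates, using the pooled two-proportion formula at 80% power, n per arm before and after 20% dropout:

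- 10% vs 30%: 62 and 78
- 20% vs 40%: 82 and 103
- 30% vs 50%: 93 and 117
- 34% vs 53.4%: 102 and 128

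In these four cases, power at 23 per arm is 26% to 39%.

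**The case against.** The strongest reply is that the article is open about its construct. It calls the endpoint demand, defines it as perceived or expressed need, and sizes the trial on it using willingness trials. Expressed demand is a defensible primary endpoint, and all three items are collected, so self-reported diagnosis could be tabulated without new data. This stands, and it is why the fix does not replace the primary endpoint. It does not remove the mismatch, because the aim and the expected conclusion are worded as diagnosis or participation.

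A reader might also infer more than the document supports:

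- **That nurses make the bookings, so the programme itself fulfils the plan item.** Phase 2 says they assist and guide, and the woman and her family still decide.
- **That accepting appointment cards inflates demand.** Within the union it changes little, since a woman with an appointment would normally count already through the plan item. The article also does not say whether the card shows a booking or an attended visit. The card matters once completed diagnosis is analysed alone.
- **That an unreported diagnosis can never come to light.** The targeted check covers only women who report one, but sections 2.10.1 and 2.11 provide for checking case report forms against source documents.
- **That demand alone makes the trial a success.** Pregnancy outcomes are also primary, and no rule is stated for whether one or both must be met.
- **That the planned effect is likely to be spurious.** That needs 59% of otherwise non-demanding women to say yes with no gain in uptake. At 10%, the chance of significance is only about 7%.

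**Conclusion.** The concern holds as a mismatch between aim and primary endpoint. Followed as written, the plan could support a conclusion about participation from a difference in willingness and plans alone, with no listed outcome to show otherwise. That logical point needs no assumed rate.

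Its size does. Under 34% control demand and equal uptake, the chance of a significant demand result at 23 per arm runs from about 7% (10% of non-demanding intervention women say yes) to about 78% (59% do). The top of that range is the planned 38.8-point effect in full. The document does not show which point in the range is realistic.

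**What to change.** - Keep demand as the primary endpoint, because section 2.3 is built on it, and limit the aim and conclusion for that endpoint to expressed demand in the Abstract, section 2.1 and the Discussion.
- Add as first secondary endpoint: prenatal diagnosis completed in the index pregnancy, confirmed by a procedure or laboratory report and checked in records for all 58 women whatever they report. An appointment card should not count as proof of completion.
- Report the three demand components separately by arm.

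**Cost.** A record check for 58 women, and a plain statement that the trial is not powered for completed diagnosis, so that result should be read through its estimate and confidence interval. Making completed diagnosis primary would be the stronger design for the stated aim. Under the assumed rates in step 4 of the working, however, it would need 78 to 128 women per arm instead of 29, so it is a trade-off and not a simple correction.

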#### Secondary outcomes

2.8.2

**Health knowledge and birth defect prevention knowledge awareness**

The awareness of health knowledge and birth defect prevention knowledge is measured through a self-designed questionnaire. Participants are asked to respond to questions about their understanding of relevant health knowledge and preventive measures, thereby assessing their level of awareness.

**Obstetric complications**

In this study, participants were asked to indicate whether they experienced the following obstetric complications: gestational hypertension, postpartum hemorrhage, and low-quality infants. Each complication was self-reported by the participants to provide a comprehensive understanding of their childbirth experience.

**Patient health questionnaire-4, PHQ-4**

The Patient Health Questionnaire-4 (PHQ-4) is a concise instrument developed to evaluate two primary dimensions of mental health: anxiety and depression. It consists of four items, the first two entries are designed to assess depressed mood, while the last two are used to assess anxiety, each rated on a 4-point Likert scale, with response options ranging from 0 (not at all) to 3 (nearly every day). Participants are instructed to consider their experiences of anxiety and depression over a specified time frame. The cumulative score ranges from 0 to 12, with elevated scores indicating increased symptom severity. This scale is user-friendly and facilitates healthcare providers in promptly identifying individuals potentially experiencing anxiety or depression, thereby enabling rapid initial assessments. The PHQ-4 has demonstrated robust internal consistency, evidenced by a Cronbach’s alpha of 0.82, highlighting its reliability for clinical application (30).

**Decisional conflict dcale, DCS**

The Decisional Conflict Scale (DCS), originally developed by O’Connor et al., is a widely acknowledged instrument for evaluating the extent of decisional conflict experienced by patients (31). In 2017, a team of Chinese researchers, including Li Yu et al., undertook the translation of the scale into Chinese, with the translated version achieving a Cronbach’s alpha of 0.897, indicating high internal consistency (32). The Chinese version of the DCS consists of 16 items, categorized into three principal dimensions: Information and Values (items 1–6), Decision Support and Decision Effectiveness (items 7, 9–11, 13–16), and Decision Uncertainty (items 8, 12). The scale employs a 100-point scoring system, where lower scores denote reduced decisional conflict. A score of 25 or higher suggests the presence of decisional conflict, while scores exceeding 37.5 may indicate potential delays in the patient’s decision-making process.

**Decision self-efficacy scale**

The Decision Self-Efficacy Scale, developed by Canadian nursing scholar O’Connor, is designed to evaluate an individual’s confidence in making informed healthcare decisions (33). The Chinese version, translated by Wang Sitong et al., was specifically applied to patients with primary liver cancer (34). This scale includes 11 items within a single dimension, each scored on a 5-point Likert scale ranging from “very unconfident” to “very confident”. The overall score is calculated by summing the individual item scores, averaging them (dividing by 11), and then multiplying by 25, resulting in a total score range from 0 to 100. Higher scores reflect greater decision self-efficacy. Studies have demonstrated the scale’s strong reliability and validity, with a content validity index of 0.966 and a Cronbach’s alpha of 0.918.

**Family health scale-short form, FHS-SF**

The Family Health Scale-Short Form (FHS-SF), developed by Crandall et al. (2020) is designed to assess family health (35). For our study, we used the Chinese version of the FHS-SF, which was translated by Wang et al. (2022). They demonstrated that this version possesses strong internal consistency and excellent test-retest reliability, confirming its validity as a reliable tool for evaluating family health (36). The scale includes four dimensions and a total of 10 items: family/social and emotional health processes, family healthy lifestyles, family health resources, and external social support. Participants rated each item on a five-point scale, ranging from “strongly disagree” to “strongly agree”. For three items related to “family health resources”, which were negatively worded, scores were reversed. The final Family Health Score is derived by summing the responses, with higher scores indicating better family health, and the total score ranging from 10 to 50.

**Decision-making participation satisfaction scale**

The Decision-Making Participation Satisfaction Scale, created by Xu Xiaolin, evaluates satisfaction with involvement in decision-making. It consists of 16 items across four dimensions: Information (4 items), Communication and Consultation (4 items), Decision-Making (3 items), and Overall Satisfaction and Confidence (5 items) (37). Participants rate each item using a 5-point Likert scale, with responses ranging from “very dissatisfied” to “very satisfied”. The total score, which ranges from 16 to 80, is calculated by summing the ratings, with higher scores reflecting greater satisfaction with decision-making participation. The scale has a Cronbach’s alpha of 0.899.

### Data analysis

2.9

This study uses IBM SPSS Statistics 24.0 software for quantitative analysis to ensure the accuracy and reliability of the statistical data. In terms of descriptive statistics, we present the baseline characteristics of the participants, with continuous variables being summarized by means and standard deviations or medians and interquartile ranges, while categorical variables are presented as frequencies and percentages. This statistical approach effectively summarizes the basic information of the sample, providing a solid foundation for subsequent analysis. The distribution of continuous data will be tested for normality. Normally distributed data will be presented as mean ± standard deviation (M ± SD), and non-normally distributed data as median (IQR). The Mann–Whitney U test will be used to compare changes in scale scores between baseline and endpoint between the two groups, while the Wilcoxon test will compare differences within each group. The chi-square test will compare the demographic characteristics of the two groups. Statistical significance will be set at p < 0.05, using a two-sided test.

In the case of missing data, assumed to be missing at random, baseline variables will be used as auxiliary variables, and missing data will be imputed using multiple imputation methods. Linear regression and logistic regression will be used for analysis, and the final combined analysis will complete the imputation process.

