### Outcome measures

2.8

There is a total of nine outcomes in the study. Medical staff will use the Questionnaire Star web platform to distribute the questionnaire, and patients will complete the questionnaire online and be instructed by medical staff either in person (at the time of hospitalisation) or by telephone (after discharge). Patient demographic information will be collected through the case system and self-designed questionnaires. (**Table 1**)

**Table 1 T1:** Data collection components and collection timeline.

Type of research	Data collection component	Content	Timepoint	Month 3	After delivery
			Month 0		
Quantitative research	Sociodemographic variables	Sex, age, insurance status, place of residence, average monthly household income, educational level, parents’ education level, area of domicile,	✓		
	Demand for prenatal diagnosis	Willingness for diagnosis, plans for prenatal diagnosis within six months, or having undergone diagnosis	✓	✓	✓
	Pregnancy outcomes	Full-term birth, preterm birth, miscarriage, induced labor due to social factors, and induced labor due to chromosomal abnormalities	✓	✓	✓
	Health Knowledge and Birth Defect Prevention Knowledge Awareness	Self-designed questionnaire	✓	✓	✓
	Obstetric Complications	Gestational hypertension, postpartum hemorrhage, and low-quality infants.	✓	✓	✓
	Depression and anxiety	Patient Health Questionnaire-4 (PHQ-4)	✓	✓	✓
	Decisional Conflict	Decisional Conflict Scale (DCS)	✓	✓	✓
	Self efficacy	Decision Self-Efficacy Scale	✓	✓	✓
	Family Health	Family Health Scale-Short Form (FHS-SF)	✓	✓	✓
	Satisfaction	Decision-making participation satisfaction scale		✓	✓

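### Secondary scale scores: a valid but inefficient rank test on change ignores baseline adjustment, cannot be computed for satisfaction, and is not reconciled with the regression named after multiple imputation

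*Protocol article*

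**What the plan says.** Section 2.9 (Data analysis) names one between-group test for scale scores: the Mann–Whitney U test "will be used to compare changes in scale scores between baseline and endpoint between the two groups". It continues: "while the Wilcoxon test will compare differences within each group". Normality testing decides only whether data are summarised by mean and SD or by median and IQR; no parametric or baseline-adjusted comparison depends on it.

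The next paragraph of section 2.9 deals with missing data. Values are multiply imputed, and "baseline variables will be used as auxiliary variables". It then says: "Linear regression and logistic regression will be used for analysis, and the final combined analysis will complete the imputation process". How this relates to the rank tests is not stated.

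In Table 1 (section 2.8), knowledge, PHQ-4, DCS, decision self-efficacy and FHS-SF are ticked at Month 0, Month 3 and after delivery. The row for the "Decision-making participation satisfaction scale" is blank at Month 0 and ticked only at the two later visits. Section 2.8.2 gives that scale a summed total of 16 to 80, so it is a scale score like the others.

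**The concern.** There are three separate problems.

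- **Precision.** Outside the imputation, baseline scores enter the comparison only by subtraction. Subtracting the whole baseline is optimal only when follow-up tracks baseline almost perfectly. Otherwise it adds baseline noise to the outcome. In a trial of 58 women this can cost appreciable power on the psychological and decision outcomes.
- **Satisfaction.** The stated test needs a baseline-to-endpoint change, and this scale has no baseline.
- **Imputation.** Section 2.3 allows for 20% dropout, so imputed data will matter. It is not settled whether a scale is analysed by a rank test on change, by a linear regression after imputation, or by a rank test whose results must somehow be combined across imputed data sets.

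In addition, *endpoint* is not tied to a visit, although the scales are measured at two follow-up times.

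**Working it through.** **Inputs from the protocol.** Two-sided alpha 0.05, power 80%, 1:1 allocation, demand proportions 72.8% and 34%, 23 per arm before dropout and 29 after (section 2.3).

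**Inputs assumed, because the protocol gives none.** Correlation rho between baseline and follow-up of 0.3, 0.5 and 0.7; equal SDs at both times; normal scores; a true effect of 0.7 SD.

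**1. The plan's own figure.** With unpooled variance, n = (1.960 + 0.842)² × (0.728×0.272 + 0.34×0.66) / 0.388² = 22.02, so 23 per arm. Then 23/0.8 = 28.75, so 29. Both stated figures reproduce. They concern the binary demand outcome; no sample size is given for the scales.

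**2. Variance.** In units of the outcome variance, a change score has variance 2(1−rho) and a baseline-adjusted follow-up score has 1−rho². The ratio adjusted/change is (1−rho²)/[2(1−rho)] = (1+rho)/2.

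| rho | change, 2(1−rho) | adjusted, 1−rho² | ratio |
|---|---|---|---|
| 0.3 | 1.40 | 0.91 | 0.65 |
| 0.5 | 1.00 | 0.75 | 0.75 |
| 0.7 | 0.60 | 0.51 | 0.85 |

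At rho of 0.5 or below, 2(1−rho) is at least 1, so the change score is no more precise than the follow-up score alone.

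**3. Patients needed.** Under normality the rank test has efficiency 3/π relative to the t-test. The planned test therefore needs (π/3) × 2/(1+rho) times as many women as adjusted regression for equal power: 1.047×1.538 = 1.61 (rho 0.3), 1.047×1.333 = 1.40 (0.5) and 1.047×1.176 = 1.23 (0.7). Matching 23 per arm under regression takes about 37, 32 and 28 per arm.

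**4. Detectable effect** at 80% power and 23 per arm. Let k = 2.802×√(2/23) = 0.826. For regression the effect is k√(1−rho²); for the rank test on change it is k√[2(1−rho)]/√(3/π). Rank test versus regression, in SD units: 1.00 versus 0.79 (rho 0.3), 0.85 versus 0.72 (0.5), 0.66 versus 0.59 (0.7).

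**5. Simulated power** for a 0.7 SD effect, Mann–Whitney on change versus regression on arm and baseline:

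| rho | 23 per arm | 29 per arm |
|---|---|---|
| 0.3 | 47% vs 67% | 58% vs 79% |
| 0.5 | 62% vs 76% | 71% vs 84% |
| 0.7 | 83% vs 90% | 91% vs 95% |

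With no true effect, the planned test rejected in 4.2% to 5.4% of simulated trials, so it holds its level.

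**6. Satisfaction.** Section 2.9 requires a difference from baseline; Table 1 supplies no Month 0 value. Neither the between-group change nor a within-group baseline-to-endpoint Wilcoxon test can be computed.

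**7. The regression sentence.** If it describes the outcome analysis, as its reference to analysis followed by a combined result suggests, scales have a second analysis that differs from the rank test, and nothing says which is definitive. If it describes the imputation models, as its place in the missing-data paragraph allows, the rank test remains the outcome analysis. That test yields no coefficient and standard error to pool by the usual combination rules.

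**The case against.** The strongest reply is that nothing here is an error of inference. Comparing changes between randomised arms by a rank test is legitimate, type I error is near 5%, and only secondary outcomes are involved. The endpoints in section 2.8.1 and the sample size in section 2.3 do not depend on it. All of that stands.

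The size of the loss also rests on a correlation and an effect that the protocol does not give. At 29 per arm, which imputation could preserve, with rho 0.7, the gap is only 91% versus 95%. Skewed scores such as PHQ-4 could narrow it. That stands too; the direction of the efficiency ranking under the stated assumptions does not change.

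A reader might infer more than the text supports:

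- *That satisfaction has no valid analysis at all.* The same test on follow-up scores is an obvious extension. Only the stated change-score version is impossible.
- *That two rival outcome analyses are definitely planned.* The regression sentence can be read as naming imputation models, so this is an ambiguity.
- *That within-group Wilcoxon results will be taken as evidence of effect.* The protocol lists them beside a between-group test and makes no such claim.
- *That baseline data are otherwise unused.* They also serve as auxiliary variables in the imputation.

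**Conclusion.** The point holds as an avoidable loss of precision plus two wording faults, all on secondary outcomes.

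- **Precision.** The baseline-adjusted effect has 0.65 to 0.85 of the change-score variance for rho 0.3 to 0.7. For an assumed 0.7 SD effect with normal scores, this means a power loss of about 7 to 20 percentage points at 23 per arm and about 4 to 21 at 29 per arm. The loss is large only if the correlation is low to moderate.
- **Satisfaction.** The mismatch between section 2.9 and Table 1 needs no assumption.
- **Imputation.** The sentence needs correcting on either reading, but the text does not settle which reading is meant.

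The documents do not support calling the planned test invalid, and they give no reason to revise the sample size on this account.

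**What to change.** In section 2.9:

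1. Make linear regression of the follow-up score on arm and that scale's baseline score the main analysis, identical in observed and imputed data, with estimates pooled by the usual rules. Report the adjusted mean difference with its 95% CI, using robust or bootstrap standard errors if scores are skewed.
2. Fix one timepoint for this analysis. The sponsor should state whether *endpoint* means Month 3 or after delivery.
3. For satisfaction, compare follow-up scores between arms with no baseline term.
4. State separately which models are used to impute and which to analyse.
5. Keep Mann–Whitney on change as a sensitivity check where a baseline exists, and label the within-group Wilcoxon tests as descriptive.

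The cost is wording only: no new data, visits or participants, and linear regression is already named in the protocol. The change should be made before outcome data are seen.

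### No between-arm analysis is tied to the primary endpoint of demand, and demand recorded at Month 0 has no stated role in it; adjusting for it is nearly free, with a power gain that may be small

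*Protocol article*

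**What the plan says.** All references are to the protocol article.

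- **Primary outcomes (2.8.1):** "The primary endpoints are the demand for prenatal diagnosis and pregnancy outcomes". Demand is binary: "A participant is considered to have a screening demand if they answer “yes” to at least one of the following three questions". The three items are willingness, a plan within six months, and diagnosis already done. The section adds: "Demand is measured at the individual level both before and after the intervention". Table 1 ticks demand at Month 0, Month 3 and after delivery.
- **Sample size estimation (2.3):** 72.8% against 34%. "Using a two-sided test with α = 0.05, β = 0.2, and power (1-β) = 80%, the sample size ratio between the two groups is 1:1", and "it was determined that 23 participants per group would be required". A 20% dropout allowance takes this to 29 per group, 58 in all.
- **Data analysis (2.9):** Mann-Whitney U is for between-group change in scale scores, and Wilcoxon for differences within a group. For categorical data: "The chi-square test will compare the demographic characteristics of the two groups". Baseline variables are mentioned again only as auxiliary variables for multiple imputation. Linear and logistic regression are named in that same missing-data paragraph, with no outcome and no covariate.
- **Randomization and blinding (2.4):** one sorted list of random numbers, alternate positions to each arm, no stratification.
- **Exclusion criteria (2.2):** women who have already had prenatal diagnosis are excluded. Women who are merely willing or planning are not.

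**The concern.** The endpoint that sizes the trial is the one for which the analysis section names no comparison. The scales are compared on change from baseline, so baseline is used for secondary outcomes, while the baseline value of the primary endpoint is collected and given no role beyond imputation.

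This matters because a woman who is willing or planning at entry already counts as a yes and cannot gain one. If more such women fall into one arm by chance, the arms differ on the outcome itself before treatment starts. An unadjusted comparison carries that difference into the result. If baseline demand predicts later demand, ignoring it also leaves explainable variation in the error. With 58 women, neither effect can be assumed negligible.

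**Working it through.** **1. The plan's own figure.** Inputs from 2.3: p1 = 0.728, p2 = 0.34, two-sided α = 0.05, power 80%. Unpooled formula:

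n = (1.960 + 0.842)² × [p1(1 − p1) + p2(1 − p2)] / (p1 − p2)² = 7.849 × (0.1980 + 0.2244) / 0.388² = 7.849 × 0.4224 / 0.1505 = 22.02, rounded up to 23.

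23 / 0.80 = 28.75, rounded up to 29. Both stated figures reproduce, and the formula is an unadjusted comparison of two proportions. By exact enumeration, the unadjusted Pearson chi-square has power 78.4% at 23 per arm and 85.8% at 29.

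**2. Chance imbalance at baseline.** Baseline prevalence is not in the document; 34% is assumed, equal to the control rate. The SD of the between-arm difference is √(2 × 0.34 × 0.66 / n):
- n = 29: √(0.4488 / 29) = 0.124, or 12.4 points
- n = 23: √(0.4488 / 23) = 0.140, or 14.0 points

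In simulation, a gap of 15 points or more arises in about 21% of trials at 29 per arm and 27% at 23. The unadjusted estimate moves by about r times the gap, where r is the baseline to follow-up correlation. At r = 0.4 a 15-point gap shifts it by about 0.4 × 15 = 6 points.

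**3. Power with and without adjustment, by common correlation.** Simulated trials at 72.8% versus 34% (20,000 per setting), unadjusted chi-square against a Cochran-Mantel-Haenszel test stratified by baseline demand. The correlation is not in the document, so a range is shown:

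| r | 23 per arm | 29 per arm |
|---|---|---|
| 0 | 78.5% → 76.8% | 85.9% → 85.5% |
| 0.2 | 78.2% → 77.8% | 85.9% → 86.9% |
| 0.3 | 78.7% → 80.0% | 85.6% → 88.9% |
| 0.4 | 78.5% → 83.4% | 85.8% → 91.3% |

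Type I error of the stratified test at 34% in both arms is 4.7% to 4.9%. In the intervention arm r cannot exceed about 0.44 at these rates: (1 − 0.728) × 0.34 / √(0.198 × 0.2244) = 0.0925 / 0.2108.

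**4. The same, by persistence.** Control-arm r is not capped at 0.44, so persistence (the chance that a baseline yes is still a yes at follow-up) was also varied, given as intervention/control:
- 90%/80%: 78.3% → 87.6% at 23 per arm (+9) and 85.9% → 93.9% at 29 (+8). The implied r is (0.90 − 0.728) × 0.34 / 0.2108 = 0.28 in the intervention arm and (0.80 − 0.34) × 0.34 / 0.2244 = 0.70 in control.
- 90%/60%: about 78% → 81% at 23 per arm.
- 85%/60%: gain of about 2 points at 23 per arm and 3 at 29.
- 80%/50%: no gain at 23 per arm.

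**5. Range.** Steps 3 and 4 together give about -2 to +9 points at 23 per arm and about 0 to +8 at 29.

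**The case against.** The strongest reply is that the protocol states no between-arm analysis of demand, adjusted or not. Sizing on two proportions does not commit the analysis to being unadjusted, and covariates are often settled in an analysis plan, which is not shown here. The Data analysis section also says that logistic regression will be used, and the abstract lists chi-square tests without a target. This stands in part. A reader might infer that the trial has ruled out adjustment; the documents do not support that. What remains is that the section does allocate tests, passes over the primary endpoint, and states a use for baseline variables only in imputation.

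A reader might also infer a loss of about ten points of power. That follows only from the 90%/80% persistence case, which implies that just (0.34 − 0.34 × 0.80) / 0.66 = 10% of control women without baseline demand acquire it. Under other plausible values most or all of the gain disappears.

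Similarly, it is tempting to say that the intervention must convert 0.388 / 0.66 = 59% of women without baseline demand. That assumes every baseline yes persists. At 90% persistence the figure is (0.728 − 0.34 × 0.90) / 0.66 = 64%. Neither rests on data in the protocol.

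Two further points stand. Because women with prior diagnosis are excluded, baseline demand reflects only willingness or plans, so its prevalence need not equal 34%. And chi-square tests of baseline demographics are uninformative under randomisation, but they change no trial result and are not part of this point.

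**Conclusion.** The point holds as a precision and clarity issue. No between-arm analysis is tied to binary demand, and a baseline value of that endpoint, already planned for collection, has no stated role in it. An unadjusted comparison would be valid: randomisation keeps it unbiased on average, and a claim of bias would go too far.

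The exposure is chance imbalance, with an SD of about 12 points at 29 per arm if baseline demand is 34%, and a possible loss of power. The power difference at the design effect is about -2 to +9 points at 23 per arm and about 0 to +8 at 29. Where it falls depends on baseline prevalence and persistence, which the protocol does not give. That baseline demand is strongly prognostic is plausible, since it is the same item in the same woman, but it is an assumption. This is a cheap improvement, not an error that invalidates the design.

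**What to change.** State in the Data analysis section that the primary between-arm analysis of demand is at Month 3, the end of the 12-week intervention, in all randomised women. Use either a Mantel-Haenszel risk difference stratified by baseline demand, or logistic regression adjusted for baseline demand and reported as a standardised risk difference, with a 95% CI in either case. Name the same model as the one fitted in the imputed data sets, so that the logistic regression in the missing-data paragraph has an outcome and a covariate. Confirm that the Month 0 answer is recorded before the woman opens her allocation envelope.

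The cost is wording only: no new data, visits or participants, since Table 1 already schedules the item. The downside is up to about 2 points of power at 23 per arm if baseline demand turns out not to be prognostic.
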